#### Stage 2: Feasibility of FIRM

2.1.2

After conducting the RCT in 3 core hospitals, the FIRM program will be tested in 6 community-based local hospitals (Chungbuk National University Hospital, Gyeongsang National University Hospital, Kyungpook National University Hospital, Presbyterian Medical Center, Dongguk University Ilsan hospital, and Chonnam National University Bitgoeul Hospital). The aim of this stage is to determine the feasibility and effectiveness of FIRM by applying the same protocol to all participating patients without randomization.

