### Sample size

2.3

According to the preliminary and unpublished data of a pilot study, the mean difference and standard deviation of Koval walking ability (as a primary outcome) were 1.034 and 1.075, respectively. To detect a mean difference in the Koval walking ability grade of 0.5 for the FIRM group (0 for the conventional group and −0.5 for the control group) with at least 80% power and a significance level of 0.05 using a 2-tailed test, each group must include 85 patients (255 in total). To allow for 10% attrition, our aim is to recruit 94 patients per group (282 in total). PASS version 14.0 (NCSS, Kaysville, UT) was used to calculate the required sample size.

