### Outcome measures

2.7

The following demographic data will be collected at baseline: age, sex, fracture location and laterality, type of surgery, and underlying disease. Functional outcomes will be measured at 1 (before intervention) and 3 weeks (after 2 weeks’ intervention), 3, 6, and 12 months after operations.

The primary outcome of this study will be Koval walking ability scores^[11]^ (range: 1–7; with a higher score indicating a worse outcome), which rates physical functioning according to walking dependency. The secondary outcomes will be as follows: physical functioning and walking ability, assessed according to the functional ambulatory category^[12]^ (range: 0–5; a lower score indicates a worse outcome) and the modified Rivermead mobility index^[13]^ (range: 0–40; a lower score indicates a worse outcome); balance and fall risk, assessed using the Berg balance scale^[14]^ (range: 0–56; a lower score indicates a worse outcome); cognition, evaluated using the Korean version of the Mini-Mental State Examination^[15]^ (range: 0–30; a lower score indicates a worse outcome); mood, evaluated using the Korean version of the Geriatric Depression Scale^[16]^ (range: 0–30; a lower score indicates a worse outcome); quality of life (QOL), evaluated using the Euro Quality of Life Questionnaire 5-dimensional classification^[17]^ (EQ-5D; range: 0–1; a lower score indicates a worse outcome); ADLs determined using the Korean version of the modified Barthel index^[18]^ (range: 0–100; a lower score indicates a worse outcome) and the Korean version of the Instrumental ADL^[19]^ (range: 0–3; a higher score indicates a worse outcome); and frailty assessed based on fatigue, resistance, ambulation, illnesses, and loss of weight (FRAIL) using the Korean version of the FRAIL scale^[20]^ (K-FRAIL; range: 0–5; a lower score indicates a worse outcome). Functional assessments will be conducted with the control group via telephone surveys performed at the same time points but measures will be limited to the Koval and EQ-5D. The adherence and drop-out rates of the program will be monitored during stage 2, in which FIRM will be applied in the community-based hospital system. Each researcher charged with outcome evaluation at each of the 3 core hospitals will work on standardizing all measuring protocols by arranging a consensus meeting before the start of the study. Regular meetings to discuss ways to unify the measurement methods will then be held.

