### Data analysis

2.8

Data will be collected using a standardized data entry form and entered into the data management system. The intention-to-treat principle will be used for data analysis. Participant characteristics will be described using means and standard deviations for continuous data and frequencies and percentages for categorical data. The 3 groups will be compared using an analysis of variance (ANOVA) or the nonparametric equivalence Kruskal–Wallis test if required. To compare paired data (intragroup) between 2 different points, we will use repeated-measures ANOVA and Friedman tests for continuous and nonparametric data, respectively. Statistical significance will be defined as a *P* value < .05. All statistical analyses will be performed using SPSS version 19.0 for Windows (IBM Corp, Chicago, IL).

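### The Friedman test is assigned to comparisons of two time points, where it reduces to the sign test and is not the counterpart of repeated-measures ANOVA (minor)

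*Protocol article*

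**What the plan says.** The within-group analysis is set out in one sentence of the Data analysis section (2.8): "To compare paired data (intragroup) between 2 different points, we will use repeated-measures ANOVA and Friedman tests for continuous and nonparametric data, respectively". Neither the Wilcoxon signed-rank test nor the sign test is named anywhere in the article.

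Four other places bear on the point:

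- **Visits.** Outcome measures (2.7) schedules five assessments: 1 week, 3 weeks, and "3, 6, and 12 months after operations".
- **Scale.** The same section states: "The primary outcome of this study will be Koval walking ability scores". These are grades from 1 to 7. Several secondary scales are much finer, such as the Berg balance scale (0–56), the modified Rivermead mobility index (0–40) and the modified Barthel index (0–100).
- **Between-group analysis.** This is specified separately in 2.8: "The 3 groups will be compared using an analysis of variance (ANOVA) or the nonparametric equivalence Kruskal–Wallis test if required".
- **Stage 2.** Section 2.1.2 plans to assess feasibility and effectiveness in community hospitals "by applying the same protocol to all participating patients without randomization".

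**The concern.** The sentence names a task, two time points within a group, and gives it a nonparametric test meant for three or more repeated measurements. At two points that test sees only the direction of each patient's change. A one-grade and a four-grade recovery in walking ability then count the same.

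The parametric method in the same sentence, repeated-measures ANOVA, becomes the paired t-test at two points and does use the size of change. Moving an outcome from the parametric to the nonparametric branch would therefore also discard the magnitude of change, which the wording does not signal. What is at stake is some power, and clarity about what is being tested, in the within-group comparisons of Stage 1 and in any within-patient change reported from Stage 2.

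**Working it through.** **The plan's own figure.** The article gives no power or sample size for any within-group test, so there is nothing to reproduce. The 85 per group in Sample size (2.3) is for a between-group difference. It is used below only as a plausible number of patients.

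**Step 1: Friedman at two points.** Let n₊ patients go up, n₋ go down and t be unchanged, with n = n₊ + n₋ + t and k = 2.

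- Each patient who changes contributes ranks 1 and 2; each unchanged patient contributes 1.5 and 1.5.
- The rank sum at the second visit is 2n₊ + n₋ + 1.5t. Its expected value is 1.5n, so the deviation is (n₊ − n₋)/2. The first visit has the same deviation with opposite sign.
- Uncorrected statistic: 12/[nk(k+1)] × sum of squared deviations = (12/6n) × 2 × (n₊ − n₋)²/4 = (n₊ − n₋)²/n.
- Tie correction: 1 − 6t/[nk(k² − 1)] = 1 − 6t/6n = (n − t)/n.
- Corrected statistic: (n₊ − n₋)²/(n − t) = (n₊ − n₋)²/(n₊ + n₋), on 1 degree of freedom.

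This is the square of the large-sample sign-test z. Over 500 simulated data sets with tied grades from 1 to 7, the largest discrepancy between the two expressions was 1.3 × 10⁻¹³. Exact or continuity-corrected sign-test p-values differ slightly.

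**Step 2: power at n = 85, two-sided 5%.** The SD is 1.075, from Sample size; treating it as the SD of within-patient change is an assumption. The shifts and the shapes of the distributions are also assumptions. Each cell rests on 2000 runs, so its standard error is at most √(0.25/2000), about 1.1 points.

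| Distribution of change | Shift | Friedman/sign | Signed-rank | Gain (points) |
|---|---|---|---|---|
| Normal, fine scale | 0.2 | 28.0% | 37.2% | 9.2 |
| | 0.3 | 54.3% | 71.8% | 17.5 |
| | 0.4 | 78.5% | 92.0% | 13.5 |
| | 0.5 | 92.3% | 98.8% | 6.5 |
| Normal, rounded to whole grades | 0.2 | 33.6% | 37.2% | 3.6 |
| | 0.3 | 63.0% | 68.7% | 5.7 |
| | 0.35 | 74.2% | 81.2% | 7.0 |
| | 0.4 | 86.4% | 90.5% | 4.1 |
| | 0.5 | 96.9% | 98.6% | 1.7 |
| Heavy-tailed (Laplace) | 0.2 | 58.5% | 53.4% | −5.1 |
| | 0.25 | 76.3% | 73.2% | −3.1 |

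At a mean whole-grade change of 1.034 both tests have about 100% power. With no shift, both reject in about 5% of the normal and rounded runs. Separate runs on bounded scales gave gains of about 2 to 8 points on Koval-like grades and 5 to 11 points on fine scales.

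**Step 3: what the signed-rank test costs.** With skewed changes the two tests have different null hypotheses:

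- Skewed continuous changes with median 0: rejection 5% (sign) against 33% (signed-rank).
- Whole grades with 30% improving and 30% worsening, the worsening by larger steps: 5% against 60%.
- Whole grades with 45% improving by one grade and 25% worsening by larger steps: 59% against 9%.

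The first two are not false positives under a null of no change at all, because the two visits are not exchangeable there. They show that the signed-rank test answers a different question once symmetry fails.

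**The case against.** The strongest reply is that the wording is merely loose. Both named methods are normally used for three or more repeated measurements, and five visits are planned. If an overall test across visits was meant, repeated-measures ANOVA and Friedman are proper counterparts and only the phrase about two points is wrong. This is plausible, but it does not remove the need for a correction: on that reading no nonparametric test is specified for a two-visit comparison.

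Second, the sign test is defensible for an ordinal scale. The signed-rank test must treat a move from grade 6 to 5 as comparable with a move from 2 to 1; the sign test needs only direction. This stands, and is why the sign test should remain as a named fallback.

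A reader might also infer three stronger things that the documents do not support:

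- **That the signed-rank test is a free gain.** It is not: it loses power with heavy tails and changes the hypothesis under skewness.
- **That the loss is the full one implied by the sign test's asymptotic efficiency of 2/3.** That ratio applies to normal changes, whereas the plan sends continuous data to repeated-measures ANOVA. For Laplace changes the ratio is 4/3, in favour of the sign test. On whole grades the gain is a few points.
- **That Stage 2 has no other functional comparison open to it, so its conclusions are at risk.** The article does not exclude comparison with Stage 1 patients, it names adherence and drop-out as what is monitored in Stage 2, and it gives no Stage 2 sample size. Power at 85 patients cannot be carried over.

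**Conclusion.** The point holds as a minor one. As written, the plan gives two-visit comparisons a test that is the large-sample sign test and is not the nonparametric partner of the method beside it.

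Under the assumed shifts at n = 85, naming the signed-rank test would gain about 2 to 8 points of power on Koval-type grades and about 5 to 18 on fine scales with near-normal changes. The upper end of the second range is the less likely one in practice, since near-normal changes on a fine scale would tend to stay in the parametric branch. The gain is nil if changes are as large as 1.034, the only mean difference the pilot data supply; the article does not say whether that figure is within or between groups.

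The effect is confined to secondary within-group tests, including any within-patient change reported from Stage 2. The between-group comparison uses ANOVA or Kruskal–Wallis, and the sample size rests on a between-group difference. Neither depends on the Friedman test.

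**What to change.** Replace the single sentence in Data analysis by two statements, for example:

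*Change over the five visits within a group will be tested overall by repeated-measures ANOVA or, for outcomes analysed nonparametrically, by the Friedman test. Any comparison of two visits will use the paired t-test or, for outcomes analysed nonparametrically, the Wilcoxon signed-rank test; where changes are clearly skewed the sign test will be used instead.*

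Reporting the median or Hodges–Lehmann change with a 95% confidence interval beside the signed-rank p-value would show the size of change directly.

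The cost is a sentence or two, with no extra data and no change to the sample size. The downside is the added assumption that changes are roughly symmetric and can be ranked across the scale, with some loss of power if they are heavy-tailed. Naming the fallback in advance limits the first of these and avoids a choice of test after the results are seen.

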### Patient and public involvement

2.9

Patients and public were not involved in the development of the research question and the selection of outcome measures. However, this research project started with a problem-solving clinical research of the government with public interest. Because the importance of comprehensive management and rehabilitation of hip fracture patients has been recognized as a major social issue, this study can fully reflect the needs of the public.

### Ethics and dissemination

2.10

The study will be performed in accordance with the relevant guidelines of the Declaration of Helsinki, 1964, as amended in Tokyo, 1975; Venice, 1983; Hong Kong, 1989; and Somerset West, 1996.^[21]^ Written informed consent for all interventions and examinations will be obtained at patient admission. The Ethics Board will be informed of all serious adverse events and any unanticipated adverse effects that occur during the study. The study protocol has been registered at Clinicaltrials.gov and will be updated. The study methods are in accordance with the SPIRIT guidelines for reporting randomized trials.^[22]^ Direct access to the source data will be provided for monitoring, audits, Research Ethics Committee/IRB review, and regulatory authority inspections during and after the study. All patient information will be coded anonymously, with only the study team having access to the original data. The study results will be disseminated in peer-reviewed publications and conference presentations.

## Discussion

3

Loss of functional independence, which is a long-term sequela of hip fracture,^[23]^ is often accompanied by a deterioration in health-related QOL.^[24]^ Longitudinal studies have shown a decline in the functional status of patients with hip fractures following reductions in rehabilitation services.^[25]^ Conversely, the long-term functional outcomes of patients who received comprehensive rehabilitation in recent clinical trials performed after hip fracture surgery included significantly better mobility and ADL scores.^[7,26,27]^ However, the dissemination of a well-designed rehabilitation program to community-based hospitals is challenging. Our study examines the efficacy of FIRM, a postoperative comprehensive rehabilitation program, and investigates the feasibility of its use in community hospitals with the goal of subsequently implementing it and evaluating its efficacy on a nationwide basis to confirm the findings.
